### Blinding

The OHC professionals who perform the intervention cannot be blinded for the allocation of participants to the intervention group, because they will need to know when to apply the intervention. Also the OHC professionals who are not trained in the participatory supportive RTW program will be informed when a participant is allocated to their team for usual OHC. Randomisation of participants will take place on participant level and participants of both the control group and the intervention group will receive OHC by OHC professionals working at the same office. Therefore, blinding the professionals for the randomisation result is impossible.

Because participants need to be informed at least briefly about the content of usual OHC and the participatory supportive RTW program before they are able to sign an informed consent, they can as well not be blinded for the randomisation result. Also blinding the participants for the outcome measures will be impossible, as most of the outcomes are self-reported. Bias caused by a lack of blinding will however be limited for the measurement of the duration until first sustainable RTW, the primary outcome measure of this study, and the duration of the sickness absence period, as in addition to the questionnaires the SSA database will be used to measure these outcomes.

To guarantee blinded analyses of the collected data by the researcher, the data will be entered into a database by a research assistant using a unique research number for each participant.

### Contamination

Since the intervention teams will not be involved in the guidance of control group participants, contamination will be limited. However, since trained and non-trained OHC teams are working at the same department, non-trained professionals could still be influenced in their usual practice by the intervention teams. Contamination of usual care and the participatory supportive RTW program may also appear when participants have already received usual OHC before they are assigned to the intervention group. Therefore, sick-listed workers who have already received usual OHC cannot participate in the study.

### Statistical analysis

After randomisation, participants will remain in the group (intervention group or control group) they are allocated to, according to the intention-to-treat-principle. Descriptive statistics will be used to check for dissimilarities of prognostic factors in the two groups at baseline. If necessary, analysis will be adjusted. A comparison of intention-to-treat-analysis to per-protocol analysis will be used to determine whether protocol deviations might have caused bias. All statistical analysis will be performed at participant level.

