### Sample size

Time to first sustainable RTW in a competitive job is the primary outcome measure for the power calculation. Based on a recent study on a participatory RTW intervention for temporary agency workers and unemployed workers with musculoskeletal disorders [22] a Hazard Ratio (HR) of 2.0 is assumed to be the minimal clinical and societal relevant ratio. This indicates that the participants in the intervention group RTW twice as quickly compared to the participants in the control group. Furthermore, it is assumed that a minimum of 2/3 of the participants will achieve first sustainable RTW during the first twelve months of the follow-up period [22]. Based on a power of (1-β=) 0.80 and a two-sided significance level of 0.05 (α) a sample size of 100 participants (n = 2 x 50) is needed. Next, potential clustering of cases guided by the same team of OHC professionals is taken into account. To correct for potential clustering of cases an ICC of 0.05 is used and the minimal number of teams is assessed: eight teams of OHC professionals who are trained in guidance according to the participatory supportive RTW program and eight teams of OHC professionals who deliver only usual OHC. Furthermore, based on comparable research [47], a loss to follow-up of 20% is expected. This results in a requisite number of 172 participants (n = 2 x 86).

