### Randomisation procedure

Randomisation will take place on participant level. In line with previous research by Vermeulen et al. [21] pre-stratification of participants is based on information about type of worker before reporting sick, i.e. unemployed worker, temporary agency worker or fixed-term contract worker. To ensure an equal distribution of control group participants and intervention group participants in the three different SSA districts, participants will also be pre-stratified on district-level. Schemes with random permuted numbers will be used by the principal investigator to generate separate block randomisation tables with fixed block sizes of four.

Randomisation takes place during the intake appointment at the SSA office. After the informed consent form is signed and the baseline questionnaire is completed by the participant, the assistant of the SSA contacts the research assistant at the VU Medical Centre to perform the randomisation. The research assistant of the VU Medical Centre uses the block randomisation table of the correct stratum to determine the randomisation result. The participant will be informed immediately about the randomisation result, intervention or control group, and the consecutive steps. Participants who are allocated to the intervention group will be assigned to an intervention team of the corresponding SSA office for guidance according to the participatory supportive RTW program in combination with usual OHC. These intervention teams will not be involved in the guidance of control group participants. Control group participants will be assigned to a team of the corresponding SSA office that is not familiar with the intervention program.

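### Adjustment of the primary Cox model depends on observed baseline imbalance, a rule that gives no criterion and would normally leave out the two stratification factors

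*Protocol article*

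**What the plan says.** The rule on covariates is in the Protocol article, Statistical analysis: "Descriptive statistics will be used to check for dissimilarities of prognostic factors in the two groups at baseline. If necessary, analysis will be adjusted". No criterion for dissimilarity or necessity follows, and no factors are listed.

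The Randomisation procedure section sets two stratification factors. First, "pre-stratification of participants is based on information about type of worker before reporting sick", with three types (unemployed, temporary agency, fixed-term). Second, "participants will also be pre-stratified on district-level", with three districts. Blocks have a fixed size of four.

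The Effect evaluation part of the Statistical analysis section describes the primary Cox model as a comparison of intervention with control and adds only that clustering within occupational health care teams will be allowed for. Neither place names worker type or district as a model term.

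**The concern.** Under sound randomisation, baseline differences between arms are due to chance. A covariate earns its place in a Cox model by predicting the outcome, not by happening to differ between arms. A rule triggered by imbalance selects on the wrong property and settles the primary model only after the baseline data have been seen.

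It also works against the design. Worker type and district were judged important enough to stratify on, and stratified blocks keep them balanced, so they are among the factors least likely to trigger adjustment. If they predict return to work, leaving them out makes the test somewhat conservative and costs power. The trial is sized for 80% power at a large effect, so it has little power to spare.

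**Working it through.** **1. The plan's own figures.** Inputs, all from Sample size: "a Hazard Ratio (HR) of 2.0 is assumed to be the minimal clinical and societal relevant ratio"; "a minimum of 2/3 of the participants will achieve first sustainable RTW during the first twelve months of the follow-up period"; power 0.80; two-sided alpha 0.05; eight teams per arm; 20% loss; and "To correct for potential clustering of cases an ICC of 0.05 is used".

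- Events (Schoenfeld): 4 × (1.960 + 0.842)² / (ln 2)² = 65.4, so 66.
- Participants: 66 / (2/3) = 99, against the plan's "a sample size of 100 participants (n = 2 x 50) is needed".
- Clustering, with n/8 participants per team: n = 50 × [1 + (n/8 − 1) × 0.05], so n = 47.5 / 0.6875 = 69.1 per arm.
- Loss: 69.1 / 0.80 = 86.4, against 86 per arm (172 in total).

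The sample-size arithmetic reproduces. The issue lies only in the analysis rule.

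**2. Simulation.** 100 participants (the size before inflation for clustering and loss), 3 × 3 strata, permuted blocks of four, two thirds with an event, 3,000 trials per scenario. Team clustering was not simulated. The article gives no prognostic strengths, so these are assumed:

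- Worker type: log-HR 0, 0.2, 0.4 or 0.6 per level. Between the extreme types the HR is exp(0.4) = 1.49, exp(0.8) = 2.23 or exp(1.2) = 3.32.
- District: half the worker-type log-HR per level.
- Three further covariates: log-HR 0, 0.2, 0.3 or 0.4 per SD.
- Conditional rule: adjust for any of the three covariates whose standardised difference exceeds 0.25 (assumed trigger); strata not in the model.

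Power (%) at a covariate-conditional HR of 2.0:

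| Prognosis | Unadjusted | Conditional rule | Strata always in | Strata + 3 covariates |
|---|---|---|---|---|
| None | 79.9 | 79.1 | 81.1 | 80.9 |
| Weak | 75.9 | 75.7 | 77.5 | 80.5 |
| Moderate | 67.0 | 68.3 | 70.9 | 79.0 |
| Strong | 56.9 | 58.5 | 65.5 | 79.4 |

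Monte Carlo standard error is about 0.7 to 0.9 points. Conditional rule against strata always in:

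- Weak: 77.5 − 75.7 = 1.8.
- Moderate: 70.9 − 68.3 = 2.6.
- Strong: 65.5 − 58.5 = 7.0.

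The no-prognosis row also shows 81.1 − 79.1 = 2.0, where no real gain is expected. That gap reflects simulation noise and a slightly more liberal test, so the weak-scenario figure cannot be told apart from zero.

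Type I error (%) at HR 1.0:

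| Prognosis | Unadjusted | Conditional rule | Better of those two | Strata in | Strata + 3 covariates |
|---|---|---|---|---|---|
| None | 4.7 | 4.9 | 5.2 | 5.3 | 6.1 |
| Weak | 4.9 | 4.9 | 5.8 | 5.9 | 6.8 |
| Moderate | 4.1 | 3.7 | 4.9 | 5.7 | 5.7 |
| Strong | 3.4 | 2.5 | 4.0 | 5.6 | 5.6 |

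**3. How often chance decides the model.** With 100 participants, the standard error of a standardised difference is 2/√100 = 0.20. P(|Z| > 0.25/0.20) = 0.211, so with three independent covariates 1 − 0.789³ = 0.51, which agrees with the simulated 50% to 52%. On all 172 randomised, the standard error is 2/√172 = 0.1525, P(|Z| > 1.64) = 0.101, and 1 − 0.899³ = 0.27.

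At HR 2.0, the unadjusted and conditionally adjusted analyses disagreed on significance in 4.8% (weak), 8.3% (moderate) and 10.2% (strong) of trials.

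**The case against.** The strongest objection is that this is a condensed article and model terms are commonly left to a fuller document. That stands in part. A reader might infer that the stratification factors are excluded from the analysis; the article does not say so, and an analysis plan could add them. What does not depend on silence is the stated adjustment rule, which would normally pass over factors balanced by design.

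Other stronger readings also go too far:

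- **An unblinded team choosing the model.** The Blinding section intends blinded analysis by the researcher, using coded data. This limits steering. It does not remove the dependence on the data, since the check still compares the two groups.
- **A 34% to 40% chance of a spurious imbalance.** This follows from testing 8 to 10 independent factors at 5% (1 − 0.95⁸ = 0.34; 1 − 0.95¹⁰ = 0.40). The article names descriptive statistics only, with no test and no number of factors.
- **A biased hazard ratio.** In the simulations the unadjusted HR averaged 1.93, 1.81 and 1.69 under weak, moderate and strong prognosis. This is largely non-collapsibility: marginal and conditional HRs are different quantities, and the article does not say which its 2.0 is.
- **False-positive inflation.** Taking the better of the unadjusted and conditional analyses gave at most 5.8%.

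It is also fair to object that adjustment is not free. The seven-term model had a type I error of 5.6% to 6.8%.

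**Conclusion.** The point holds in a limited form. The article fixes a rule that lets observed imbalance decide the covariates of the primary model, without a criterion or list, and that rule would normally omit worker type and district.

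Against a model that always includes the strata, the loss is about 2, 3 or 7 points of power under weak, moderate or strong prognosis, and essentially nothing if the factors are not prognostic. Only the strong case stands well clear of the 2-point gap seen with no prognosis at all. Part of each gap reflects the conditional rule's conservatism (type I error down to 2.5%) set against a slightly liberal comparator.

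Against the strata plus three predictors, the gaps are larger: 4.8, 10.7 and 20.9 points. They rest on the assumed covariate strengths and are flattered by that model's liberal Wald test.

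All sizes depend on the assumed prognostic strengths, the 0.25 SD trigger and reading HR 2.0 as conditional. The case for changing the rule rests as much on removing discretion as on power.

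**What to change.** In Statistical analysis, delete the sentence that allows adjustment if necessary and keep the baseline table descriptive. State that the primary Cox model, whatever the observed balance:

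- is stratified by, or adjusted for, worker type and district;
- accounts for clustering by team;
- includes at most two or three named baseline predictors already collected, for example age, baseline 4DSQ distress and the intention to return to work recorded at screening.

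Adjust repeated questionnaire outcomes for their baseline value where one exists. Table 1 shows none for the Work Limitations Questionnaire.

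The change is to wording and needs no new data. It has two statistical costs. First, the list must stay short: worker type and district as covariates take four terms, so three predictors make seven, the size that gave the slightly liberal test. The plan's information amounts to about 66 events after allowing for clustering (172 × 0.80 × 2/3 = 91.7 expected events, divided by a design effect of 1 + (8.6 − 1) × 0.05 = 1.38, gives 66). Second, the reported HR becomes conditional on the covariates and should be labelled so.

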#### Effect evaluation

The duration until first sustainable RTW in a competitive job in both groups will be described by using the Kaplan-Meier method. The Cox proportional hazard model will be used to estimate differences in RTW between the intervention group and the control group, expressed in hazard ratios (HR) for sustainable RTW and the corresponding 95% confidence intervals. Differences between both groups in total number of days at work and total days of sickness benefit during follow-up will be analysed with a general linear model. Differences in other secondary outcome measures will be analysed with the use of longitudinal random coefficient analysis. Clustering of participants within the OHC teams will be taken into account.

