### Outcomes

#### Effect evaluation

The primary outcome measure is the duration until first sustainable RTW in competitive employment. This is defined as the duration in calendar days from the day of enrolment in the study until first sustainable RTW in a competitive job for at least 28 consecutive calendar days without partial or full recurrence of sickness absence. In line with Crowther et al. [25], competitive employment is defined as a full or part-time position held by the worker in a regular work setting, for which payment is received at the market rate.

According to the Dutch Sickness Benefit Act, recurrence of an accepted sickness benefit claim within 28 calendar days after ending of the previous benefit is considered as belonging to the preceding sickness benefit period, on condition that it is due to the same (or related) disorder. Although for sick-listed workers without a permanent employment contract ending of the sickness benefit not automatically results in RTW, it was chosen to mark RTW as sustainable only when the participant returned to work for at least these 28 calendar days.

RTW data, i.e. work resumption in regular (paid) work, are registered continuously by the Dutch SSA and will be collected from the SSA database after twelve months follow-up.

In addition, with a self-administered questionnaire the participant will be asked whether he or she has worked in (un)paid labour in the last three months. If the participant did RTW, he or she will be asked to specify the period in which RTW has taken place and the average working hours per week.

Secondary outcome measures are:

– *RTW in any type of work*

 In addition to the primary outcome measure, the duration until first RTW in any type of work will be measured, i.e. paid work, unpaid work and work with ongoing supportive benefit.

– *Duration of the sickness benefit period*

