 For workers without a permanent employment contract, it is possible that the sickness benefit ends, before full RTW is achieved. The worker can be recovered from illness or functional limitations (assessed with regard to last or previous work) without actual RTW, because the worker has no workplace to return to. Therefore, in line with Vermeulen and colleagues, the duration of the sickness benefit period will be assessed as well. This is defined as the duration of the sickness benefit from the day of enrolment until ending of the sickness benefit for at least 28 consecutive calendar days [21]. Additionally, the total number of days of sickness benefit during follow-up will be calculated. Awarded sickness benefit claims during follow-up are only included in the calculation when the participant is sick-listed due to the same (or related) mental disorder [21]. Data on sickness benefit will be collected from the SSA database and by self-report of the participants.

– *Work status*

 Work status is defined as the average number of hours worked per week during the one-year follow-up. In addition to a self-administered questionnaire, the SSA database will be used to collect this information.

– *Severity of mental disorder symptoms*

 Severity of mental disorder symptoms will be assessed using the Four-Dimensional Symptom Questionnaire (4DSQ) [34].

– *Perceived general health status*

 Using the Dutch translation of the SF-36 [35] perceived general health status will be measured.

– *Quality of life*

 Quality of life will be measured using the Dutch translation of the Euroquol questionnaire [36].

– *Attitude, Social influence, and self-Efficacy (ASE)*

 For the development of earlier participatory RTW programs the Attitude-Social influence-self-Efficacy (ASE) model was used as an underlying theoretical framework [37,38]. In these studies the ASE constructs were assessed using a questionnaire developed by Van Oostrom and colleagues [39]. In this study we will make use of the same questionnaire.

– *Work limitations*

 Work limitations will be measured with the Dutch translation of the Work Limitations Questionnaire (WLQ) [40].

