Quality of life (Euroqol)	X		X		X
ASE determinants (ASE questionnaire)	X		X		X
Work limitations (WLQ)			X		X
Health care utilization (Tic-P)	X	X	X	X	X
Patient satisfaction* (PSOHSQ)		X			

*Patient satisfaction with occupational health care services is only measured in the intervention group (as part of the process evaluation).

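### The catch-all analysis sentence assigns two right-censored durations (first return to any work, end of sickness benefit) to a repeated-measures model that does not handle censoring

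*Protocol article*

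**What the plan says.** The effect evaluation under Statistical analysis allocates methods in four steps.

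- Kaplan-Meier: "The duration until first sustainable RTW in a competitive job in both groups will be described by using the Kaplan-Meier method".
- Cox: results are "expressed in hazard ratios (HR) for sustainable RTW and the corresponding 95% confidence intervals".
- Linear model: differences in "total number of days at work and total days of sickness benefit during follow-up will be analysed with a general linear model".
- Everything else: "Differences in other secondary outcome measures will be analysed with the use of longitudinal random coefficient analysis".

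Team clustering is to be taken into account.

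The effect evaluation under Outcomes lists the secondary measures. For return to any work, "the duration until first RTW in any type of work will be measured". Benefit duration is "the duration of the sickness benefit from the day of enrolment until ending of the sickness benefit", where the ending must last at least 28 days. Total benefit days over follow-up is introduced afterwards as an additional quantity. For hours, "Work status is defined as the average number of hours worked per week during the one-year follow-up". The remaining measures are questionnaire scales: 4DSQ, SF-36, Euroqol, ASE and WLQ.

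**The concern.** Time to first return to any work and time to end of benefit have the same structure as the primary outcome: a clock starting at enrolment, one event, and a cut-off at one year. The primary outcome gets survival methods, but by the wording these two do not. They fall into the remainder, whose method suits scales measured at several visits.

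Both durations bear directly on how the primary result is read. The protocol itself explains that benefit can end without the worker having a job to go to, which is why benefit duration is assessed separately. If the stated rule is followed, the analyst must improvise a value for everyone without an event. If it is not followed, the method is chosen after the data are in. Either way the result is not prespecified, and it would not be on the hazard ratio scale used for the primary outcome.

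**Working it through.** **Step 1. Set each outcome beside the method the text gives it.** Sources: the two effect evaluation subsections and Table 1.

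| Outcome | Value per person | Censored at 12 months | Method by the text |
|---|---|---|---|
| Sustainable return to competitive work (primary) | one time | yes | Kaplan-Meier, Cox |
| First return to any work | one time | yes | remainder: random coefficient |
| End of sickness benefit | one time | yes | remainder: random coefficient |
| Total benefit days | one total | no | linear model |
| Work status (average weekly hours over the year) | one average as defined | no | remainder: random coefficient |
| Days at work | not a listed outcome | – | linear model |
| 4DSQ, SF-36, Euroqol, ASE | baseline, 6 and 12 months | no | remainder: random coefficient |
| WLQ | 6 and 12 months | no | remainder: random coefficient |

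The remainder rule suits the last two rows. It does not suit rows two and three, and it does not match work status as defined.

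**Step 2. What a random intercept model does with one value per person.** The model splits the variance as Var(y) = between-person variance + residual variance. With a single value per person only the sum is identified, and there is no slope over time. In a simulated set of 138 people with one value each, the fit gave 40.075 + 40.075 = 80.150, and ordinary least squares gave a residual variance of 80.150. The split is arbitrary, and the analysis reduces to an ordinary linear comparison of the recorded values.

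- For work status this is degenerate but not biased.
- For a duration it means a linear comparison of recorded days with no censoring indicator. The text does not say what is recorded for someone without the event.

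**Step 3. Could the linear model sentence rescue benefit duration?** No. That sentence names total benefit days, and the outcomes text presents the total as additional to the duration. They are two quantities, and only the total is covered.

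**Step 4. Is the sample size touched?** Inputs from Sample size: HR 2.0, two-sided alpha 0.05, power 0.80, two thirds with the event, ICC 0.05, eight plus eight teams, 20% loss.

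- Events (Schoenfeld): 4 × (1.96 + 0.84)² / (ln 2)², rounded up, is 66. Then 66 / (2/3) = 99, against the stated 100.
- Clustering over 16 teams: N = 100 × [1 + (N/16 − 1) × 0.05], so N = 95 / 0.6875 = 138.2.
- Loss: 138.2 / 0.80 = 172.7, against the stated 172.

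The calculation reproduces and rests on the primary outcome alone, so reassigning secondary methods leaves it unchanged.

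**The case against.** **The Cox sentence may be meant broadly.** It opens by speaking of differences in return to work, which could take in any kind of work. But it then restricts the hazard ratios to sustainable return, and the outcomes section uses that term for the primary outcome. Benefit duration is not return to work at all, so this reading cannot cover it.

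**This is a condensed article and an analysis plan may exist.** That would answer a gap. Here an explicit rule is stated, and it names an unsuitable method.

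**Table 1 marks benefit duration at all five time points.** It marks the primary duration in the same way, and that is analysed by Cox. The marks show when data are collected; they do not turn one duration into five.

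**A linear comparison need not be wrong.** This stands in part. If everyone were followed for the full year and non-events were entered as 365 days, a linear comparison would estimate the restricted-mean difference. The protocol does not state that convention, and it expects 20% loss to follow-up. The SSA register is described as covering regular paid work, so the unpaid part of return to any work appears to depend on questionnaires.

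Three stronger readings are tempting, and the document does not support them.

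- A reader might infer a bias in days by borrowing the primary outcome's event rate and dropping people without an event. No rule says they are dropped. No censoring rate is given for these durations, and the wider definition of return to any work points to less censoring than for the primary outcome.
- A reader might infer that work status has no repeated data. Table 1 collects it at T0 to T4, so hours per interval could be modelled longitudinally; only the outcome as defined is a single average.
- A reader might infer that the WLQ cannot be modelled at two visits, or is valid only among people at work. The text specifies no random slope, and a random intercept model belongs to the same family. Nothing in the protocol restricts who answers the WLQ.

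**Conclusion.** The point holds on the plain text. Time to end of sickness benefit is misassigned on any reading; time to first return to any work is misassigned on the natural reading. Both are single right-censored event times placed under a method for repeated measures. In addition, the outcome and analysis lists do not match on work status and days at work.

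Severity is moderate. No numerical error can be attached, because it would depend on censoring rates and a handling rule that the protocol does not give. The primary outcome has suitable methods, total benefit days has a workable one, the questionnaire scales are correctly placed, and N = 172 is unaffected. The conclusion assumes only that the catch-all sentence means what it says.

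**What to change.** Reword the effect evaluation paragraph under Statistical analysis.

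- Assign Kaplan-Meier and Cox, with the same handling of team clustering as the primary outcome, to the time to first return to any work and the time to end of sickness benefit.
- Limit longitudinal random coefficient analysis, by name, to 4DSQ, SF-36, Euroqol, ASE and WLQ.
- Reconcile work status. Either assign the general linear model to the yearly average of weekly hours as defined, or state that interval hours from T1 to T4 are modelled longitudinally.
- Define days at work as an outcome, or delete it from the analysis sentence.

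If a separate analysis plan exists, check that it carries the same allocation. The cost is one paragraph of wording, with no new data and no change to the sample size.
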